## Abstract

**Background:**

While patient involvement in mental health care is repeatedly stressed in policy documents, there are actually few studies that evaluate person-centred care interventions within psychiatric services. We present here the design and planned evaluation of an educational intervention for inpatient staff involved in the care of persons with schizophrenia and similar psychoses.

**Methods/design:**

The care intervention will be assessed using a non-randomised trial with a before and after approach. The intervention involves an educational and experimental learning phase for hospital staff, followed by an implementation phase. The intervention is multi-professional; psychiatrists, psychiatric nurses, psychiatric carers, social workers, occupational therapists, and a medical secretary will be engaged in a participatory approach where they practice how to create a partnership and explore recovery-related goals together with patients. Patient-related outcomes include empowerment and satisfaction with care. Ward-level outcomes include daily ward burden, length of inpatient stay, and number of days with involuntary care. In addition, qualitative methods will be applied to capture patient, next-of-kin, and staff perspectives.

**Discussion:**

The care intervention is expected to contribute to the improvement of inpatient care for persons with severe and complex mental health issues.

**Trial registration:**

The trial was retrospectively registered at ClinicalTrials.gov June 9, 2017, identifier: NCT03182283.

## Background

Schizophrenia affects approximately 1% of the population and, because it is often associated with early onset and long term, severe disability, it has a major impact on Disability-Adjusted Life Years worldwide [1]. For the families of persons with schizophrenia, the burden of care is great [1–3].

The treatment of schizophrenia rests on three cornerstones: 1) pharmacological treatment with the lowest effective dose of anti-psychotic medication, 2) psychological and psychosocial treatments, and 3) social support [2]. Treatment with anti-psychotics is often a prerequisite for symptom control. While patients and their relatives alike recognize this, they experience that too much focus on pharmacological treatment can hamper the initiation of other treatment elements, and lead to feelings of powerlessness and resignation [4]. Further, care outcomes of importance for the patient may differ from those commonly utilized in traditional medical treatment settings [5].

A systematic review highlighted the need for research on patient involvement and the organization of care for persons with schizophrenia [6]. The report stressed the importance of increased involvement in the care process on the part of service users and their families. This theme has been reiterated in policy statements from a number of Western countries during the past decade [7], yet a large gap exists between these recommendations and real world practices [8].

### Person-centred care

The concept of person-centred care has a long history. Introducing the term in the 1940s, Carl Rogers [9] highlighted three important principles: every person possesses considerable qualities, can make use of available resources, and can find a way to remedy difficulties. Many definitions of person-centred care have been proposed since then, and there is to date no clear consensus definition [10]. A recent overview of reviews on the person-centred care concept [11] identified six components of person-centred care: establishing a therapeutic relationship, sharing power and responsibility, getting to know the patient as a person, working to empower the person, creating and working with trust and respect, and communicating understandable and accurate information. We define person-centred care according to these components throughout the present paper.

Person-centred care outcome studies have been conducted in a variety of patient populations and settings [12–14], but relatively few research studies target inpatient psychiatric services. Out of 34 publications identified in a recent review relating to person-centred care in psychiatric inpatient settings [15], only 16 were described as involving original research. Most of these did not evaluate person-centred care interventions but instead described nurses’ caring approaches, the development of self-report measures, and evaluations of specific information tools.

Three studies that evaluated person-centred care interventions were included in the review [15], one was described as an original research paper, the other two as practice development papers although they reported on intervention outcomes. The first study [16], reported on a series of person-centred care interventions implemented at 58 different psychiatric emergency and inpatient psychiatric units. The person-centred care interventions were associated with a reduction of seclusion and restraint use. The second study [17] also reported on person-centred care interventions and these were associated with culture change, a restraint-free environment, and less medication. The third study [18], was conducted at an inpatient psychiatric unit in which a person-centred care intervention was implemented. The intervention was associated with increased client and caregiver satisfaction, a better understanding of the client’s situation, and improved team ability to document a person-centred care plan. One of the three outcome studies included patients with schizoaffective disorder [17] although the study did not specifically target patients with a psychosis diagnosis. The other two studies [16, 18] did not report diagnostic categories. Therefore, it is unclear if the intervention outcomes can be reproduced in inpatient psychosis populations.

There are some studies indicating that persons with psychoses, despite having symptoms that might make it especially difficult for this group to actively participate in their care, also might benefit from person-centred care interventions. A systematic review and meta-analysis that focused specifically on shared treatment decision-making and patient empowerment in both in- and outpatient settings where at least half of the participants had a psychosis diagnosis showed small beneficial effects of increased shared decision-making on treatment-related empowerment [8]. Focusing specifically on treatment for persons with a psychotic illness, a randomized controlled study involving outpatients, case managers, relatives, and other significant persons in a person-centred Resource Group model showed improved social function and consumer satisfaction both at two [19] and five year [20] follow-ups.

### Aim

Considering the lack of studies specifically targeting inpatient care for persons with schizophrenia and similar psychoses, we wanted to develop and test an educational intervention for staff working in hospital services for persons with schizophrenia and similar psychoses (Person-Centred Psychosis Care, PCPC). We describe here the design and planned evaluation of the staff educational program. Specific research questions include: 1) Will the intervention have effects on empowerment and satisfaction with care in persons with schizophrenia and similar psychoses? 2) Will the intervention have effects at the ward level (duration of inpatient care, daily overall ward burden, involuntary care measures such as use of physical restraints and forced injections)? 3) What are the experiences of the care and the intervention as narrated by persons with schizophrenia and similar psychoses, by their next-of-kin, and by hospital staff?

## Methods/design

A before and after design will be used to explore quantitative outcomes of the PCPC intervention. In addition, the narrated experiences of the care and the intervention will be described.

### Participants and setting

All participants will be recruited from the Psychosis Clinic at Sahlgrenska University Hospital, Gothenburg, Sweden. This is the only clinic providing inpatient services for persons with schizophrenia and similar psychoses in Gothenburg, the second largest city in Sweden. The clinic has four inpatient wards with a total of 43 beds.

#### Patient sub-study

Fifty patients will be recruited before the intervention starts and fifty will be recruited when the intervention has been implemented at all four wards. The inclusion criteria for the persons with psychosis disorders will be: age ≥ 18 years fulfilling criteria for a clinical diagnosis of schizophrenia or other psychotic spectrum disorder in accordance with ICD-10 [21]. Individuals with co-morbidity will be included. Exclusion criteria include severe cognitive disability with inability to comprehend study goals and procedures (as determined by the patient’s psychiatrist), or lack of knowledge of the Swedish language to such a degree that an interpreter is required.

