#### Patient data

Shortly before planned discharge, a nurse or a psychologist included in the research group asks persons with psychosis disorders to complete research questionnaires related to outcomes and possible confounding variables (specified below). Some open-ended questions are also asked.

Since the data collection is carried out during inpatient care, all the usual management and safety mechanisms are in place. Should complications occur, these are reported at the usual clinical rounds.

The primary outcome measure is self-reported empowerment. The Empowerment Scale [29, 30] is validated and used internationally in studies involving persons with severe mental ill-health. There are 28 questions; responses are given on a Likert type scale ranging from 1 (agree totally) to 4 (disagree totally), and a higher score indicates a higher level of empowerment.

The secondary outcome measure is consumer satisfaction measured with the UKU-ConSat Rating Scale [31]. This scale contains 11 items; responses are given on a Likert type scale ranging from − 3 (very bad/negative/little) to + 3 (very good/positive/much). A higher score indicates a higher degree of satisfaction with care. The scale also contains a question on overall life experience and a question concerning mental health with the answer format 0 (worst imaginable) to 100 (best imaginable).

Possible confounders including illness burden, functional ability, and overall health are quantified for each patient at discharge. Positive and negative symptom burden are rated with the Remission sub-scale of the Positive and Negative Symptoms Scale consisting of 8 items reflecting core symptoms of schizophrenia [32]. Functional ability is determined using the GAF Scale [33] and overall health with the EQ-5D Scale [34].

Both during the pre- and post- intervention periods, experiences of care during the inpatient stay are explored in individual semi-structured interviews with a purposeful sub-sample of patients. Questions include: Please describe your experiences of the care you received. What did you perceive as helpful/problematic/difficult? Did you feel listened to? Were you included in decisions about the care?

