### Data analyses

Random data entry checks will be performed by a person who is in the research group but who is not involved with data entry to promote data quality. Missing continuous data will be dealt with in line with published instructions from the researchers who developed the different instruments. The distributions of the continuous variables will be examined to determine whether parametric (independent samples ANCOVA) or non-parametric (Mann-Whitney U-test) analyses will be employed when analysing group differences. The Chi-square test will be used to analyse dichotomised data. Two-tailed tests will be used and *p*-values less than .05 will be considered statistically significant. The focus group interview data will be analysed using methods for thematic analysis [35].

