## Discussion

The current study employs a simple before and after design. While this is recognized as an important limitation, randomised control trials are not always optimal for assessing complex interventions in everyday clinical practice [23]. Randomising individual patients on the same ward (PCPC vs. standard care) was not considered an alternative as there would be a risk for “contamination” of the standard care situation as the intervention will introduce a new way of thinking about care practices. A traditional cross-over design is not possible as the intervention includes a pedagogical intervention for staff that cannot be “unlearned”. Randomising two of our wards to intervention and the other two wards to standard care would not provide sufficient power for a cluster study, and would be difficult since patients and staff sometimes move between wards which would “contaminate” the standard care situation. For a true evaluation of the effects of a person-centred educational intervention for care staff, another type of study design is required. The appropriate design would be a trial randomised at group level, a cluster randomised trial [23] in which random allocation is done at the cluster level (i.e. at the level of the service providers).

The fact that there are relatively few research studies of person-centred care in inpatient psychiatric settings, and in mental health settings in general [36] might be explained by these kinds of design problems which might deter researchers from studying outcomes of person-centred care. The lack of studies might also in part be explained by implementation problems. Smith and Williams [36] conducted a review and identified an important barrier to operationalise person-centred care practices, “the reluctance of service providers to fully embrace the principles of person-centred care, particularly the challenge presented by ‘empowerment’” (p. 296). To better meet potential implementation problems, we will tailor the PCPC intervention to the existing care setting and use a participatory approach in which the patients, professionals, and researchers co-create the intervention to fit the specific care setting.

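### The before/after comparison names no confounder fixed before exposure to care, and its non-parametric route allows no adjustment, so a change in case mix could partly be read as an intervention effect

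*Protocol article*

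**What the plan says.** Protocol article, Patient sub-study, on how the two groups are formed: "Fifty patients will be recruited before the intervention starts and fifty will be recruited when the intervention has been implemented at all four wards". These are separate patients, not the same patients measured twice. Those eligible are adults who have a "clinical diagnosis of schizophrenia or other psychotic spectrum disorder in accordance with ICD-10 [21]. Individuals with co-morbidity will be included". Patients with severe cognitive disability who cannot follow the study, and those who need an interpreter, are excluded.

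Patient data: shortly before discharge, patients are asked to "complete research questionnaires related to outcomes and possible confounding variables (specified below"). What follows names illness burden, functional ability and overall health. They are measured by the PANSS remission sub-scale, "consisting of 8 items reflecting core symptoms of schizophrenia", and by GAF and EQ-5D, all at discharge. The word *including* introduces the list.

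Data analyses: the distributions decide whether "parametric (independent samples ANCOVA) or non-parametric (Mann-Whitney U-test) analyses will be employed when analysing group differences". No covariates are listed.

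Discussion: "The current study employs a simple before and after design". The authors call this an important limitation and say that a true evaluation of effects needs another type of design.

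**The concern.** Nothing in the design balances the two groups. There is no randomisation, no concurrent control and no described matching. The first group is recruited before the intervention, whose education phase began in December 2014. The second is recruited once all four wards have implemented it, within an implementation phase of about three years. If the share of patients with schizophrenia rather than another psychosis, the age mix or the share with comorbidity differs between periods, and these traits relate to empowerment or satisfaction, mean scores move without any intervention effect. Covariate adjustment is the only protection that the analysis can offer.

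The article does choose some confounders, but every one it names is rated after exposure to the ward's care. Such ratings can themselves be changed by the intervention, so adjusting for them may remove part of a real effect. They are also indirect stand-ins for diagnosis, age or comorbidity. At stake is the reading of research question 1: empowerment (primary) and satisfaction (secondary).

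**Working it through.** **1. Inputs from the article.** 42 per group, 80% power, two-sided .05, a .2 difference in mean empowerment (Power calculation); 50 recruited per group (Patient sub-study). No SD is given.

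**2. The plan's own figure.** Without an SD, 42 per group can be neither confirmed nor refuted. Solved backwards, a two-sample t-test with these inputs has a detectable standardised difference d = 0.619, so the implied SD is .2 / 0.619 = 0.323. This serves only to convert SD units into scale points.

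**3. Bias formula.** For a binary trait omitted from the comparison:

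bias = (gap in mean outcome between trait groups) × (shift in the trait's share between periods).

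The documents give neither quantity, so both columns of inputs below are assumptions. The noncentrality at 50 per group is bias in SD / √(2/50) = bias / 0.2. The rejection rate is for an unadjusted two-sided .05 t-test with 98 degrees of freedom and no true effect.

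| Assumed gap | Assumed shift | Bias (SD) | Scale points (× 0.323) | Share of .2 | Noncentrality | Rejection |
|---|---|---|---|---|---|---|
| 0.3 SD | 10 points | 0.03 | .010 | 5% | 0.15 | 5.3% |
| 0.5 SD | 20 points | 0.10 | .032 | 16% | 0.5 | 7.9% |
| 0.8 SD | 20 points | 0.16 | .052 | 26% | 0.8 | 12.4% |
| 0.8 SD | 30 points | 0.24 | .078 | 39% | 1.2 | 22.1% |

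**4. Does adjustment remove it?** Simulation: 8000 runs, 50 per group, no true effect, residual SD 1 within diagnosis group, unadjusted versus adjusted for the binary trait.

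| Gap | Share before → after | Unadjusted | Adjusted |
|---|---|---|---|
| 0.5 SD | 40% → 60% | 7.7% | 4.7% |
| 0.8 SD | 40% → 60% | 12.0% | 4.9% |
| 0.8 SD | 40% → 70% | 20.1% | 5.2% |

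The unadjusted rates sit slightly below step 3 because the diagnostic gap also widens the spread within each period.

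**5. Price of adjustment.** Variance inflation = 1 / (1 − r²), where r is the correlation between trait and period.
- 40% → 60%: r² = 0.2² = 0.04, inflation 1.04, standard error × 1.02.
- 40% → 70%: covariance 0.3 / 4 = 0.075; r² = 0.075² / (0.25 × 0.55 × 0.45) = 0.091, inflation 1.10, standard error × 1.05.

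This is before any gain from variance that the covariates explain.

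**6. What was not computed.** These rates describe an unadjusted comparison, such as the plan would make if it used no covariates. ANCOVA with the discharge scales was not simulated; it would depend on how closely the scales track case mix and how far the intervention moves them, and the article gives neither.

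**The case against.** A reader might infer that diagnosis, comorbidity and age will not be used, so that any case-mix change would be read as an intervention effect. The documents do not support that. The list of confounders is open, ANCOVA is planned without excluding any covariate, and a complete covariate list is commonly left to the full protocol or the SAP, which are not shown.

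Other points also stand:
- Symptom burden, function and overall health plausibly carry part of the case-mix difference, so the unadjusted rates may overstate what remains under ANCOVA.
- Both groups come from the same clinic under the same criteria, and nothing in the article suggests a large shift.
- Broad eligibility is not an error, and it is not unlimited given the exclusions.
- Comorbidity does not decide eligibility. It may not have been recorded, and participants are told that the data are anonymous, so it may not be recoverable for patients already recruited.
- The authors openly acknowledge the limits of the design.

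What the objection does not answer is narrower. The article goes beyond silence: it names a confounder set, and no member of it is fixed before exposure. Age and diagnosis are needed for eligibility but appear nowhere in the planned comparison. The Mann-Whitney route cannot adjust for anything, whatever a later document lists. Acknowledging a weak design does not settle the covariates; it makes them matter more.

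**Conclusion.** The point holds in a limited form. The article commits to no pre-exposure covariate in a non-randomised comparison of different patients, and one of its two analysis routes rules out adjustment. A change in case mix could therefore be taken in part for an intervention effect on empowerment or satisfaction.

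The size is unknown. Under the assumed gaps of 0.5 to 0.8 SD and shifts of 20 to 30 points, the bias is .03 to .08 scale points, and an unadjusted test rejects in about 8% to 22% of trials with no true effect. With a 10-point shift and a 0.3 SD gap it is negligible. These figures assume one binary trait, no other adjustment and the implied SD of 0.323. They show that material bias is possible, not that it is likely. The change is worth making because it is cheap, with medium confidence.

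**What to change.** In Data analyses, name age, sex and ICD-10 diagnosis group (schizophrenia versus other psychotic-spectrum disorder) as ANCOVA covariates for empowerment and satisfaction, to be entered whatever imbalance is observed. Add comorbidity (yes/no) where it is recorded for both groups. Tabulate these variables by period, and report the period difference with and without adjustment.

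If ANCOVA assumptions fail, use a method that keeps the covariates, such as robust, rank-based or ordinal regression, in place of an unadjusted Mann-Whitney test.

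Cost: a few sentences of analysis text; four degrees of freedom out of about 98 (three without comorbidity); and a standard error about 2% to 5% larger if the diagnostic share really shifts by 20 to 30 points, before any gain from explained variance. Age and diagnosis must already be known for every participant. Whether sex and comorbidity can be obtained for patients already recruited needs checking before they are written in.

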#### Staff sub-study

We will recruit a sample of staff members (*N* = 20) comprising persons from all four wards, across professions, and with varying age, gender, and length of employment. All members of staff willing to participate are eligible for inclusion and there are no exclusion criteria. However, practical circumstances such as being at work and being available for interviews on scheduled interview days might limit participation.

#### Next-of-kin sub-study

We will strive to include relatives of patients with varied backgrounds with regard to age, gender, ethnic background, education level, living situation (living together with the patient or not), and involuntary care. For relatives to be included, the patients must have agreed to us to contacting their next-of-kin. All relatives willing to participate are eligible for inclusion and there are no exclusion criteria.

### Power calculation

The primary outcome will be patient empowerment. A power calculation based on an independent samples t-test showed that a total sample size of 84 participants (42 per group in a balanced design) yields 80% power to detect a .2 difference in mean empowerment score between groups when “pre-intervention” and “post-intervention” scores are compared with a two-tailed test at a significance level of .05.

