The last occasion for the education intervention started with following up on the activities of change that the learning groups had performed. A discussion about what constitutes successful change followed. The learning groups then continued to work with their implementation plans. They discussed challenges, resources, and co-operation partners. They also discussed how to follow up on their short- and long-term person-centred goals. The educational intervention finished with a summary of what had been accomplished during the intervention and each learning group had a tailor-made implementation plan to follow during the implementation process.

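### Ward enters neither the power calculation nor the named patient-level tests, so a shift in ward mix can bias the before-after contrast and the 80% power is conditional

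*Protocol article*

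**What the plan says.** **Power calculation.** "A power calculation based on an independent samples t-test showed that a total sample size of 84 participants (42 per group in a balanced design" and this "yields 80% power to detect a .2 difference in mean empowerment score between groups", "compared with a two-tailed test at a significance level of .05". No standard deviation and no allowance for ward are given.

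**Participants and setting; Patient sub-study.** "The clinic has four inpatient wards with a total of 43 beds". "Fifty patients will be recruited before the intervention starts and fifty will be recruited when the intervention has been implemented at all four wards". No split or quota by ward is stated.

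**Data analyses.** The distribution of each continuous variable decides whether "parametric (independent samples ANCOVA) or non-parametric (Mann-Whitney U-test) analyses will be employed when analysing group differences". Ward is not mentioned. Under Patient data, the possible confounders named are symptom burden, functional ability and overall health; the list is open-ended and does not name ward.

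**Intervention.** Ten staff from each ward took part in the learning phase, at the end of which "each learning group had a tailor-made implementation plan to follow during the implementation process". All staff on all four wards then develop the intervention over about three years.

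**Discussion.** Randomising two wards against two is rejected partly because it "would not provide sufficient power for a cluster study". The same paragraph says that patients and staff sometimes move between wards.

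**The concern.** Patients on one ward in one period share staff, routines and whatever degree of implementation that ward has reached. Two separate problems can follow.

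- **Ward mix.** If wards differ in empowerment scores for stable reasons such as case mix, and the four wards supply different shares of the 50 patients before and after, part of the ward difference appears as a period effect.
- **Ward-by-period variation.** If wards change by different amounts between periods, the before-after difference varies more than an independent-samples test assumes. Power is then lower, and type I error higher, than stated.

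The comparison has no concurrent control, so little else guards against such a bias. Ward is a known, easily recorded variable whose mix effect can be removed by adjustment.

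**Working it through.** **Inputs from the protocol article:** 42 per group for the calculation, 50 per group for recruitment, difference 0.2 scale points, two-sided alpha 0.05, 80% power, four wards present in both periods.

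**Assumed, because not stated:** ward ICC (0.05 as the main illustration, 0.02 and 0.10 either side), and the correlation of a ward's effect before with its effect after (cluster autocorrelation, CAC), from 0 to 1.

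**1. The plan's own figure.** Solving the two-sample t-test for the SD that gives 80% power at 42 per group and a difference of 0.2 yields SD 0.323, a standardised effect of 0.2/0.323 = 0.62. A standardised difference of 0.2 would need 393 per group, so 0.2 must be in scale points. The stated size is attainable but cannot be verified without the SD. At 50 per group and SD 0.323, power is 86% if patients are independent.

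**2. Ward mix, stable ward effects (CAC 1).** Let d be the change in each ward's share of the sample. The variance of the before-after difference, relative to what the t-test assumes, is about

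1 − ICC + (n/2) × ICC × Σd², with n = 50 per group,

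and the type I error of the unadjusted test is about 2 × (1 − Φ(1.96/√ratio)).

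- Strong shift, 20/15/10/5 to 5/10/15/20: d = −0.3, −0.1, 0.1, 0.3, so Σd² = 0.20. At ICC 0.05 the ratio is 0.95 + 25 × 0.05 × 0.20 = 1.20 and type I error is about 7.4%. Simulations gave 7.1% to 7.6%. The SD of the bias is 0.323 × √(0.05 × 0.20) = 0.032 points, against a target difference of 0.2.
- Same shift, other ICCs (simulated): 5.8% at 0.02 and 9.9% to 10.0% at 0.10.
- Mild shift, 15/13/12/10 to 10/12/13/15: Σd² = 0.0208. At ICC 0.05 the ratio is 0.95 + 0.026 = 0.976, and simulated type I error is 4.7% to 5.0%, so there is no inflation.
- With ward as a fixed effect, simulated type I error under the strong shift falls from 7.1% to 4.6% (ICC 0.05) and from 10.0% to 5.2% (ICC 0.10).

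**3. Ward-by-period variation, equal ward mix.** With m = 50/4 = 12.5 patients per ward and period, the design effect is

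DE = 1 + (m − 1) × ICC − m × ICC × CAC.

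At ICC 0.05 this is 1 + 0.575 − 0.625 × CAC. Power is that of the t-test at 50/DE per group; type I error is that of the unadjusted test from the formula in step 2.

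| CAC | DE | Power | Type I error |
|---|---|---|---|
| 1 | 0.95 | 88% | 4.4% |
| 0.8 | 1.075 | 84% | 5.9% |
| 0.5 | 1.26 | 78% | 8.1% |
| 0 | 1.575 | 68% | 11.8% |

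Simulated type I error at CAC 1, 0.8 and 0 was 4.7%, 6.2% and 12.3%. At ICC 0.02 even CAC 0 leaves power at 79%. With only four wards, these power figures are somewhat optimistic.

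**4. What ward fixed effects do not do.** At ICC 0.05, CAC 0 and equal mix, simulated type I error was 12.0% without ward in the model and 12.2% with it. Adjustment cures the problem in step 2, not the one in step 3.

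**The case against.** Much of the case against a stronger claim stands.

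- A reader might apply the usual cluster inflation 1 + (m − 1) × ICC and conclude that power is really 63% at 42 per group, or that type I error is 11%. That formula is the CAC 0 extreme. All four wards contribute to both periods, so ward is crossed with period and stable ward effects cancel when the mix is equal. The unadjusted test is then slightly conservative.
- A reader might infer that ward mix does confound the result. Nothing in the article shows that the mix changes or that wards differ on empowerment; the article only fails to prevent it.
- A reader might take the Discussion as admitting that the chosen design is a cluster design. The remark about cluster power concerns a rejected randomised alternative. The article openly calls its own before-after design an important limitation.
- The tailored plans belong to cross-disciplinary learning groups that are not said to be ward-specific. Successful experiences are shared across wards, and patients and staff move between them. All of this may reduce ward-by-period variation.
- ANCOVA can carry ward, and a fuller analysis plan may list it as a covariate, so the article does not prove that ward will be ignored.

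The last point does not reach the fallback. The article itself lets the outcome distribution send the primary comparison to a Mann-Whitney test, which can adjust for neither ward nor any other covariate. Nor does it alter the power statement, which is given without its independence condition.

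**Conclusion.** The point holds in a limited form. The power calculation assumes independent patients, ward appears in none of the named patient-level tests, one of the two analysis branches cannot adjust for it, and recruitment does not hold ward mix constant. A shift in mix can therefore bias the contrast: at ICC 0.05 type I error is about 7-8% for a strong shift and near 5% for a mild one. Differing uptake by ward can reduce power at 50 per group from 86% under independence to 84% or 78% at CAC 0.8 or 0.5, and to 68% in the worst case. The margin between 42 and 50 per group keeps about 80% power up to a design effect of about 1.19.

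These sizes rest on an SD solved from the stated sample size and on assumed ICC and CAC values. The documents do not support a claim that the 5% error or 80% power is definitely wrong, or wrong in a fixed direction.

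**What to change.** - Record ward for every patient, with a rule fixed in advance for those who transfer during the stay.
- Include ward as a fixed effect (3 degrees of freedom) in the primary patient-level model.
- Replace the unadjusted Mann-Whitney fallback with a method that can adjust for ward, for example ANCOVA on ranks or a ward-stratified rank test.
- Report ward mix by period and the ward-specific before-after differences.
- State that the 80% power assumes no ward-by-period variation, and give the ICC and CAC range beside it.
- Say plainly that ward fixed effects remove confounding by ward mix but not ward-by-period variation. Four wards are too few for reliable cluster-robust errors, so the ward-specific differences have to show how far that variation matters.

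The cost is three degrees of freedom and a less favourable, conditional power statement; no extra patients are needed. If the mix did shift strongly, adjustment would also cost some precision. In the 20/15/10/5 to 5/10/15/20 example the within-ward information is 4 + 6 + 6 + 4 = 20 (each term n₀n₁/(n₀ + n₁)) against 25 when the mix is equal, so the variance factor is 25/20 = 1.25. That is the price of removing the bias, and it is close to nil when the mix is stable.
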